## Abstract

**Introduction:**

Major depressive disorder (MDD) is a chronic condition. Although current treatment approaches are effective in reducing acute depressive symptoms, rates of relapse are high. Chronic and inflexible retrieval of autobiographical memories, and in particular a bias towards negative and overgeneral memories, is a reliable predictor of relapse. This randomised controlled single-blind trial will determine whether a therapist-guided self-help intervention to ameliorate autobiographical memory biases using Memory Flexibility training (MemFlex) will increase the experience of depression-free days, relative to a psychoeducation control condition, in the 12 months following intervention.

**Methods and analysis:**

Individuals (aged 18 and above) with a diagnosis of recurrent MDD will be recruited when remitted from a major depressive episode. Participants will be randomly allocated to complete 4 weeks of a workbook providing either MemFlex training, or psychoeducation on factors that increase risk of relapse. Assessment of diagnostic status, self-report depressive symptoms, depression-free days and cognitive risk factors for depression will be completed post-intervention, and at 6 and 12 months follow-up. The cognitive target of MemFlex will be change in memory flexibility on the Autobiographical Memory Test- Alternating Instructions. The primary clinical endpoints will be the number of depression-free days in the 12 months following workbook completion, and time to depressive relapse.

**Ethics and dissemination:**

Ethics approval has been granted by the NHS National Research Ethics Committee (East of England, 11/H0305/1). Results from this study will provide a point-estimate of the effect of MemFlex on depressive relapse, which will be used to inform a fully powered trial evaluating the potential of MemFlex as an effective, low-cost and low-intensity option for reducing relapse of MDD.

**Trial registration number:**

NCT02614326.

Strengths and limitations of this studyThis early-stage platform trial seeks to establish an estimate of effect size to power a later-stage trial.The intervention condition will be compared with an active control condition.The hard-copy workbook format limits the ability to track completion of the intervention sessions in real time.The absence of booster sessions following workbook completion may limit the long-term efficacy of the intervention.

## Introduction

Depression is a recurrent and pervasive condition which dramatically reduces quality of life for the individual and costs the health system in the UK an estimated £7.5 billion per year.^1^ Although psychological approaches to treating depression are effective in reducing current symptoms,^2^ relapse rates are high. On average, those with major depressive disorder (MDD) will experience 10 separate depressive episodes across their lifespan,^3^ and symptom severity increases with each experienced episode.^4^ As such, reducing depressive relapse is a key challenge for health systems. Broadly, depressive risk is increased by the chronic use of maladaptive cognitive styles which promote depressogenic thoughts, attributions and beliefs,^5^ thus, intervention to reduce the chronicity of these cognitive styles may thereby break the vicious cycle of depression. Importantly, as cognitive risk factors for depression remain evident when depressive symptoms remit, it may be possible to complete interventions to shift these factors when the individual is psychologically well, and more able to engage in therapy. Further exploration of low-cost and low-intensity options for reducing these cognitive risk factors may have important implications for limiting depressive relapse and subsequent costs for the individual and healthcare system. This trial will investigate the efficacy of a low-intensity programme, Memory Flexibility training (MemFlex), which aims to reduce one such risk factor—inflexible retrieval of autobiographical memories.

Autobiographical memory, that is, memory of personal life experiences, is integral in forming one’s sense of self,^6^ and disruptions in autobiographical memory increase risk of depression (for review see ref^7^). Autobiographical information is stored in a fluid manner, and can therefore be retrieved in a variety of formats, including as specific, single incident events that are rich in detail (eg, when I forgot my purse and couldn’t buy my train ticket), or as generalisations that summarise consistency across a category of events (eg, catching the train to work every day). Memory flexibility refers to the ability to successfully navigate the autobiographical information database to deliberately retrieve memories varying in detail and emotional valence. In depression, flexible movement within the autobiographical information database is compromised,^8 9^ resulting in relative difficulties in retrieving both general and specific memories.^8 10 11^ This can create functional impairment as both types of memory are necessary in daily cognitive skills; for example, specific memories can help to guide problem solving^12^ while general memories encode regularities of experiences that can be used to inform judgements of the self, world and others.^13 14^ Impaired recall of specific memories is a key predictor of the first onset of depression^15^ and also of future depressive episodes in those with a history of recurrent depression (for meta-analysis see ref 16), although comparable studies examining the predictive effects of impaired generality or flexibility have yet to be carried out.

A core feature of reduced flexibility is the chronic over-retrieval of autobiographical memories that are: (1) negative in emotional valence and (2) overgeneral in nature. Regarding valence, depressive risk is increased by a habitual and inflexible inclination towards negative memories, and subsequently, a neglect for positively valenced and neutrally valenced memories.^17^ However, it is not simply that negative information is retrieved more readily, but that when positive information is recalled, it is less vivid^18^ and therefore has an attenuated impact on affect, reducing the emotional benefits that are gained from recalling positive memories.^19^ In this way, biased memory retrieval can impair the ability to repair transient low mood.^20^ In addition, the absence of vivid, positive memories of oneself and a continual emphasis on negative autobiographical information reinforces the negative self-schemata that maintain and promote depression.^21^

Difficulties in intentional autobiographical retrieval also increases risk for depression. A tendency towards general memory recollection and reduced retrieval of specific memories is evident in those with current depression, however, the overgeneral retrieval style does not remit with depressive symptoms,^11^ suggesting that reduced specific recall is a durable cognitive marker for depression^16^ that may not be shifted by current psychological treatments,^22^ though this has not yet been well explored. Repeated recall of overgeneral summaries may promote depression by reinforcing overly general (negative) attributions regarding the self (eg, I always fail) and the world (eg, the world is an unfair place). Previous research has also demonstrated that impaired retrieval of specific memories impacts a number of intermediate factors that promote depression. Abstract and overgeneral memory recall intensifies rumination,^23^ which in turn creates negative affect, impairs mood regulation, and is itself a risk factor for recurrent depression.^24^ Impaired retrieval of specific memories also reduces the ability to establish intimacy in social communication,^25^ impairs problem solving^26^ and limits the ability to appropriately restrain the overly general, negative self-judgements that are characteristic of depression.^27^

As reduced flexibility in the use of negative and overgeneral memory retrieval styles both independently promote depression symptoms^8 16^ and may also interact with other risk factors (eg, stress^28^); to trigger a depressive episode, intervening to reduce bias and improve memory flexibility may thereby reduce depressive risk. There is some evidence to suggest a positive impact of targeting these factors individually, such as by reducing overgeneral memory through memory specificity training.^29–31^ However, simultaneously targeting these factors may reduce compounded effects, and promote flexibility in the use of other depressogenic cognitive styles.^32^ In addition, explicitly training improved recall of positive, general memories (eg, of kindness, determination, caring relationships) may help to support reinitiation of the overly general, positive self-judgements that are associated with mental health (for review, see ref 33).

To this end, we have previously piloted a novel intervention which aims to improve cognitive flexibility in those experiencing recurrent depression.^34^ MemFlex uses autobiographical memory as a modality to train negative and overgeneral processing styles. The workbook-based programme is presented in eight self-guided sessions completed over a 1-month period, and involves completion of memory retrieval exercises that aim to improve concrete, specific processing, thereby reducing overgeneral, abstract processing and improve access to neutral and positive emotional material, thereby reducing negative bias. In an initial uncontrolled trial with those in remission from MDD, MemFlex was effective in reducing overgeneral memory (d=0.48), rumination (d=0.29), and cognitive avoidance (d=0.18), and also improved social problem solving (d=0.55) from preintervention to postintervention.^34^ An ongoing randomised controlled trial is comparing the effect of MemFlex to an active psychological intervention for those experiencing a current major depressive episode (see ref^35^ for trial protocol). However, results from the uncontrolled trial suggest that MemFlex may not only prove beneficial for current symptoms of depression, but also for reducing cognitive risk factors for depressive relapse.

Preliminary evidence of an effect on multiple depressive risk factors provides a solid foundation for a larger trial of MemFlex determining the efficacy of the programme in relapse prevention, against an active control group.^36^ In line with recommendations for the phase-based development and evaluation of novel interventions, we will complete an early-stage, randomised controlled platform trial with the primary aim of estimating the likely effect size of MemFlex on measures of depressive relapse, which can then be used to inform a later-stage, fully powered trial. This study will therefore estimate the effect of MemFlex on the recurrence of depression over a 12-month period, relative to an active control condition—psychoeducation. We hypothesise effect sizes in favour of MemFlex, such that individuals completing MemFlex when they are currently remitted from depression will experience a greater number of depression-free days in the 12 months following workbook completion and demonstrate a longer period of time until depressive relapse, compared with those who complete psychoeducation.

## Methods and analysis

### Study design

The design is a single-blind, participant-level randomised controlled trial comparing MemFlex to psychoeducation. All participants will provide informed consent to complete a 4-week programme, consisting of an initial face-to-face session, followed by eight self-guided workbook sessions presenting either the psychoeducation or MemFlex materials. Participants will be assessed at baseline, postintervention, at 6 months follow-up and at 12 months follow-up.

### Participants and recruitment

Inclusion criteria are a minimum age of 18 years and a primary diagnosis of MDD, as assessed using the Structured Clinical Interview for DSM Disorders (SCID^37^). On study entry, participants must not be currently experiencing a major depressive episode. That is, participants must be in partial or full remission from MDD, as indexed by the Longitudinal Interval Follow-up Evaluation (LIFE^38^) for the SCID. Additional exclusion criteria are prior completion of any autobiographical memory-based training programme, experience of another current mood disorder, psychosis, personality disorder or current drug, or alcohol dependence. Those experiencing significant cognitive impairment, as assessed through self-report (via an open-ended question asking whether the individual has ever experienced an intellectual disability or traumatic brain injury), will also be excluded. Participants may continue with any current recovery-maintenance medication or psychological interventions (eg, booster sessions, mindfulness practice) while participating in the study.

We will recruit through three avenues in Cambridge, UK. First, participants will be invited to contact us through advertisements in the general community (eg, posters in general practitioner surgeries) and the local newspaper. All those who contact us will be sent further information about the study, and invited to complete an initial telephone screening. We will also recruit from our database of participants with depression who are interested in taking part in research. All participants on this database have previously completed the SCID and meet criteria for MDD. These participants will be telephoned or emailed to make them aware of the study, and all those who express an interest in participating will complete the LIFE to determine current depression and wider diagnostic status. Finally, we will recruit patients who have expressed an interest in participating in research from local mental health services. Clinical care teams will be made aware of the study, and will be encouraged to ask their patients if they would like to take part in research. If the patient expresses an interest in research, their clinical care team will pass on our information sheet.

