### Participant allocation

Random allocation to condition using computer-generated, quasi-random numbers will completed by the trial statistician (PW), who is blind to study objectives. Once a participant has provided informed consent and completed the preintervention assessment, the researcher completing the initial session will open a sealed, opaque envelope to reveal condition allocation. This process is demonstrated in the Consolidated Standards of Reporting Trials (CONSORT) diagram (see figure 1).

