#### Primary clinical outcomes

The primary clinical outcomes are number of depression-free days from postintervention to 12-month follow-up, and number of days until depressive relapse, both according to the LIFE.

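### Entry remission status (partial or full) is likely to be strongly prognostic, but no stratification by it is described and it is not a fixed covariate in either primary analysis

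*Protocol article*

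**What the plan says.** Under Participants and recruitment, the article requires that "On study entry, participants must not be currently experiencing a major depressive episode". It explains this as "participants must be in partial or full remission from MDD, as indexed by the Longitudinal Interval Follow-up Evaluation". Partial remission is therefore admitted expressly, and the entry interview separates it from full remission.

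The section on primary clinical outcomes names "number of depression-free days from postintervention to 12-month follow-up, and number of days until depressive relapse, both according to the LIFE".

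Participant allocation reads "Random allocation to condition using computer-generated, quasi-random numbers", prepared by the trial statistician. Sealed envelopes are opened after consent and the preintervention assessment. No stratification factor is mentioned.

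The Statistical analysis plan section compares depression-free days by t-test, moving to ANCOVA if baseline differences make it necessary, and compares time to relapse by Cox regression. Baseline differences in the cognitive target, BDI-II severity, concurrent treatment or demographics are to be covaried. Residual symptoms and number of previous episodes appear as exploratory moderators. Remission status at entry appears in none of these places.

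**The concern.** A participant who has fallen below episode threshold but still has residual symptoms, and one who is fully well, start follow-up in different states. Both primary outcomes come from the same interview that rates that state at entry, so a strong association is to be expected.

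The trial's main product is an effect estimate for planning a later trial. Leaving a strong, already measured prognostic factor out of the model widens the interval around that estimate. Making adjustment conditional on an observed baseline difference means that the data decide which analysis is reported, and the article gives no criterion for when a difference is large enough. With 70 participants, appreciable chance imbalance is plausible.

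**Working it through.** **The plan's own figure.** The Power analysis section aims for 25 evaluable per condition and allows for up to 25% attrition: 25 / (1 − 0.25) = 33.3, so 34, against 35 stated. This is consistent. The section gives no SD, event rate, hazard ratio or share in partial remission, so everything below rests on assumptions.

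**Assumptions (not in the document).** Share in partial remission p = 0.40. Deficit in depression-free days for partial remitters D = 60 to 90. SD within remission group 90 days. Arms of exactly 35, or 25 among completers.

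**Chance imbalance without stratification.** With 28 partial remitters among 70, the number X in one arm is hypergeometric.
- Var(X) = 35 × 0.4 × 0.6 × 35/69 = 4.26, so SD(X) = 2.06.
- The arm difference in share is (2X − 28)/35, with SD 2 × 2.06/35 = 0.118, or 11.8 points.
- P(difference of at least 15 points) = 22%. P(at least 20 points) = 9%. The smallest split that reaches 20 points is 18 against 10, or 8/35 = 22.9 points.
- With 20 partial remitters among 50 completers: Var(X) = 25 × 0.4 × 0.6 × 25/49 = 3.06, and the SD of the difference is 14.0 points. The two probabilities are 39% and 15%.

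**Share of outcome variance.** This is p(1 − p)D² / [p(1 − p)D² + 90²].

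| p | D = 60 | D = 90 |
|---|---|---|
| 0.20 | 576/8,676 = 6.6% | 1,296/9,396 = 13.8% |
| 0.40 | 864/8,964 = 9.6% | 1,944/10,044 = 19.4% |
| 0.50 | 900/9,000 = 10.0% | 2,025/10,125 = 20.0% |

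**Shift from a 20-point imbalance.** 0.20 × 60 = 12 days and 0.20 × 90 = 18 days in the unadjusted difference.

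**Set against the standard error (p = 0.40).** The total SD is √8,964 = 94.7 or √10,044 = 100.2 days.
- At 35 per arm, the unadjusted SE is √(2 × 8,964/35) = 22.6 or √(2 × 10,044/35) = 24.0 days. Removing the variance due to remission status gives √(2 × 8,100/35) = 21.5, ignoring the one degree of freedom spent. The gain is about 5% to 10% of the SE.
- At 25 per arm, the unadjusted SE is 26.8 or 28.3 days, and 25.5 after adjustment.
- At 35 per arm the 12- to 18-day shift is 12/22.6 = 0.53 to 18/24.0 = 0.75 of one SE.

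**The case against.** **A tempting stronger reading.** A reader might infer that, because no minimum time in remission is stated, the criterion lets an unfinished index episode be scored as a relapse, so that the primary outcomes do not measure relapse at all. The document does not support going that far. The LIFE may carry its own duration convention, which cannot be seen here, and a journal article may leave such a rule to the full protocol. Depression-free days are counted from postintervention, after a four-week programme, so some early returns would fall before counting begins. Admitting partial remitters is an explicit choice. No frequency of miscounted episodes can be derived, and any calculation of a diluted hazard ratio needs the further unsupported assumption that such returns are unaffected by treatment.

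**No bias.** Randomisation spreads unstable remitters over both arms in expectation, and chance imbalance is already part of the unadjusted standard error. This stands. The shift of 12 to 18 days shows where part of that error comes from; it is not an additional error.

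**Adjustment is already planned.** BDI-II differences are to be covaried, and residual symptoms are much of what separates partial from full remission. This stands in part: adjusting for the BDI-II would recover some of the loss, so the figures above are for no adjustment at all. But that adjustment is contingent on an observed difference, and the BDI-II is a self-report score, not the interview rating that defines entry and outcome.

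**Stratification is inferred from silence.** The allocation section is brief, and the full protocol might stratify. That is possible, and it is one reason to put the model covariate first. The analysis section, by contrast, states its conditional rule outright.

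**Conclusion.** The point holds as a matter of precision and pre-specification, not of bias. A likely strong prognostic factor, rated at entry on the same instrument as both primary outcomes, is not among the listed covariates, and the stated rule makes adjustment depend on the imbalance found. On the assumed values it explains about 10% to 19% of the variance in depression-free days (7% to 20% if the partial-remission share runs from 20% to 50%). Adjustment would shrink the standard error by about 5% to 10% at 35 per arm. A 20-point imbalance, with about 9% probability at 35 per arm and 15% at 25, moves the unadjusted difference by 12 to 18 days. None of the three driving assumptions can be checked in the document, and no comparable figure can be given for time to relapse because no event rate is stated. The text does not show that the primary outcomes are invalid or that the arms are compared unfairly.

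**What to change.** 1. Name remission status at entry (partial or full, from the entry LIFE) as a covariate in an ANCOVA of depression-free days and in the Cox model for time to relapse, whether or not the arms differ at baseline. This replaces the conditional choice between t-test and ANCOVA.
2. Where allocation lists can still be changed, prepare separate blocked envelope sequences for partial and full remission. The article reports a first participant on 18 January 2016, so this may no longer be feasible. The covariate does not depend on it.
3. Reconcile the entry criterion with the population described elsewhere. The abstract says that participants "will be recruited when remitted from a major depressive episode", the Introduction argues that "it may be possible to complete interventions to shift these factors when the individual is psychologically well", and the hypothesis speaks of people currently remitted, while the criterion also admits partial remission. The sponsor should say which population the estimate describes. No minimum remission duration is proposed here.

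Cost: one extra term in each primary model and, if adopted, a second envelope list. The entry rating is already made. The Cox hazard ratio then becomes conditional on remission status, which should be stated when it is passed to the later trial.

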### Participant allocation

Random allocation to condition using computer-generated, quasi-random numbers will completed by the trial statistician (PW), who is blind to study objectives. Once a participant has provided informed consent and completed the preintervention assessment, the researcher completing the initial session will open a sealed, opaque envelope to reveal condition allocation. This process is demonstrated in the Consolidated Standards of Reporting Trials (CONSORT) diagram (see figure 1).

**Figure 1 F1:**
[figure not shown]
Flow chart of study design (Consolidated Standards of Reporting Trials diagram). All outcome and process measures will be completed at all time points. MemFlex, Memory Flexibility training.

